### HIV-HCV-HBsAg-Syphilis Self-Testing Procedure

#### Overview

HIV-HCV-HBsAg-Syphilis self-testing will be conducted using Rong Ai Jian, a WeChat-based point-of-care testing mini-program developed by the Chengdu CDC. This platform integrates CBOs engaged in HIV prevention efforts throughout Chengdu. Participants can request self-testing kits through the Rong Ai Jian mini-program on WeChat. The CBOs will mail the test kits directly to applicants, who will then complete self-testing, upload their results, and receive professional review and feedback via the platform. This mechanism has been operational for over 2 years and has demonstrated stable functionality and effectiveness in practice.

The platform provides a complete traceable workflow, ensuring the accuracy and authenticity of self-test results.

#### Kit Distribution and Coding

Each four-in-one rapid test kit is prelabeled with a unique ID number by the CBO staff before shipment.

#### Result Reporting

After completing the self-test according to the instruction sheet, participants are required to upload a clear photo of the used test kit through the Rong Ai Jian WeChat mini-program.

#### Real-time Verification

CBO staff can view the uploaded image immediately on the platform and verify the result visually. The staff will then record the verified result in the platform system by selecting “Negative,” “To Be Retested,” or “Invalid.”

#### Participant Confirmation

The verified result automatically appears in the participant’s mini-program interface. Participants can screenshot this verification and send it to their peer volunteer as proof of testing completion.

#### Referral for Confirmation

Cases marked as “To Be Retested” are treated as preliminary reactive results. Both the CBO staff and peer volunteer then refer the participant to a qualified medical institution for confirmatory testing.

#### Final Confirmation and Data Entry

Only results that are confirmed by certified laboratories (eg, by treponemal and non-treponemal tests for syphilis or confirmatory assays for HIV/HBV/HCV) are entered as positive outcomes in the research database.

### HIV-HCV-HBsAg-Syphilis Combo Rapid Testing

The study will utilize the quadruple rapid diagnostic test kit developed by Guangzhou Wondfo Biotech Co., Ltd. This assay enables the simultaneous qualitative detection of HIV-1/2 antibodies, HCV antibody, HBsAg, and Treponema pallidum antibody from whole blood, serum, or plasma samples. The test employs a lateral flow immunochromatographic assay and provides results within 15 minutes.

Each test kit includes a test cassette, desiccant pouch, dropper, and buffer vial. The HIV-HCV-HBsAg-Syphilis Combo Test is approved by the China National Medical Products Administration, ensuring its safety and efficacy for clinical application.

Independent evaluations have reported excellent diagnostic performance, with sensitivities of 99.70% for HIV, 98.71% for HCV, 98.97% for HBsAg, and 98.47% for syphilis, along with corresponding specificities of 100%, 99.33%, 99.78%, and 99.68%, respectively. This highly reliable and user-friendly assay is particularly well-suited for point-of-care testing and large-scale screening initiatives, enabling timely diagnosis and facilitating rapid linkage to appropriate health care services [22].

### Questionnaire Survey

Baseline data collection will be conducted via an online self-administered questionnaire. Assigned project volunteers will securely deliver the survey link to participants through encrypted messaging channels.

### Electronic Informed Consent

An electronic informed consent process will be embedded at the beginning of the baseline questionnaire. Participants will be required to carefully read the informed consent form, which details the purpose of the study, potential risks and benefits, data confidentiality measures, and their rights as participants. Only after acknowledging their understanding and agreement will participants be permitted to proceed with completing the survey.

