## Methods

### Ethical Considerations

Participation in this study will be entirely voluntary, and comprehensive measures will be implemented to ensure participant anonymity and data confidentiality. The study protocol has been reviewed and approved by the Ethics Committee of the Chengdu CDC (Approval No. 2024021).

All participants were required to carefully read the electronic informed consent form prior to enrollment, which will provide detailed information about the study purpose, procedures, potential risks, and benefits. Only those who voluntarily select the “Agree” option will be permitted to proceed with the questionnaire, thereby documenting their informed consent. Participants will have the right to withdraw from the study at any time without any negative consequences.

To prevent coercion or power imbalance between peers, volunteers, and participants were matched across different universities; all volunteers must sign a confidentiality agreement; all participation is anonymous and voluntary. We also conducted dedicated confidentiality training during the pre-project orientation.

To support HIV prevention efforts, the study will provide access to evidence-based online health education, individualized counseling services, and free prevention supplies, including condoms, lubricants, and HIV/STI self-testing kits. Additionally, participants will receive modest financial compensation for completing each survey, in recognition of their time and contribution. Participants received RMB 20 (US $2.83) at baseline, RMB 20 (US $2.83) at the 6-month follow-up, and RMB 20 (US $2.83) at the final 12-month follow-up.

Potential risks primarily will involve the possible inadvertent disclosure of sensitive information related to sexual behavior. However, robust data security and privacy protection protocols will be established, including data encryption, pseudonymization of identifiers, and restricted access to sensitive information, to minimize this risk.

The anticipated benefits of participation—including increased HIV-related knowledge, improved access to prevention services, and facilitation of early detection and timely linkage to care—are expected to outweigh the minimal risks involved.

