### Study Setting

This study is scheduled to commence in June 2025 and conclude in June 2026. The research process will consist of the following sequential phases: participant recruitment, HIV/hepatitis C virus (HCV)/hepatitis B surface antigen (HBsAg)/syphilis testing, baseline survey, intervention implementation, midterm survey, and final follow-up survey.

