#### Recruitment via WeChat

Recruitment information will be disseminated through a dedicated WeChat official account (WeChat is a Chinese multipurpose messaging, social media, and mobile payment app developed by Tencent Inc), which will publish targeted enrollment announcements clearly specifying the study’s inclusion criteria. These announcements will also provide the WeChat contact information of designated student volunteers. Interested individuals will be instructed to contact these volunteers directly via WeChat, where the volunteers will conduct eligibility screening and coordinate preenrollment HIV and STI testing.

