### HIV-HCV-HBsAg-Syphilis Testing

#### Overview

Participants will be required to complete self-testing for HIV, HCV, HBsAg, and syphilis at baseline, as well as during both follow-up surveys. Only individuals who test negative for HIV at baseline will be eligible for enrollment in the cohort. All participants are tested at each follow-up using a four-in-one rapid diagnostic kit that simultaneously detects HIV, syphilis, HCV, and HBV. Any reactive screening result triggers referral for confirmatory testing in certified laboratories. If a participant tests positive for any infection marker, they are immediately referred to a certified medical institution for confirmatory diagnosis and treatment, in accordance with national guidelines.

It should be specifically noted that we have also taken into account the issue of the serological window periods. To minimize potential misclassification, we have incorporated several measures including repeat testing for recent exposures and comprehensive risk documentation.

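### As written, volunteer screening and the four-marker entry self-test come before the only study consent described, and the baseline survey follows that test.

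*Protocol article*

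**What the plan says.** **Where consent sits.** The Electronic Informed Consent section states: "An electronic informed consent process will be embedded at the beginning of the baseline questionnaire". It then says what consent unlocks: "Only after acknowledging their understanding and agreement will participants be permitted to proceed with completing the survey". Ethical Considerations describes the same step. Choosing to agree means that a man "will be permitted to proceed with the questionnaire, thereby documenting their informed consent". On timing, that section says only: "All participants were required to carefully read the electronic informed consent form prior to enrollment".

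**Where screening and testing sit.** Study Setting declares an order: "The research process will consist of the following sequential phases: participant recruitment". After recruitment the list runs through the four-marker tests and ends "syphilis testing, baseline survey, intervention implementation, midterm survey, and final follow-up survey". Recruitment via WeChat says that "the volunteers will conduct eligibility screening and coordinate preenrollment HIV and STI testing". The overview of the testing section adds: "Only individuals who test negative for HIV at baseline will be eligible for enrollment in the cohort".

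**Where the questionnaire sits.** Survey Content and Follow-Up has the baseline questionnaire completed at enrollment.

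**What the questionnaire measures.** Table 1 takes the proportions tested for HIV and for STIs in the preceding 3 months from the structured questionnaire, along with intention items. It also lists knowledge measures.

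**The concern.** Two things are at stake.

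**Participant protection.** Followed as written, a man tells a student volunteer about same-sex behavior, requests a mailed kit, tests himself for four infections and uploads a photograph that community-organization staff read. Only then does he see the study's account of its risks and confidentiality terms. Ethical Considerations names inadvertent disclosure of sensitive information as the main risk, and his exposure to it starts before he is told of it. Study Design records the ethics committee's view that this group is sensitive and vulnerable.

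**Validity of the baseline.** The design is a before-after comparison, so the baseline must be free of the study's own procedures. The testing indicators ask about a 3-month window, and the entry test falls inside it if the survey comes afterward. The limitations text in the Discussion expects few incident infections and relies on behavioral indicators, HIV testing among them, as early markers of effect. A distorted baseline therefore affects an outcome the study depends on.

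**Working it through.** The article gives no figure to reproduce. The check is whether the sections fix an order, and what follows from it.

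**Step 1: rebuild the sequence.**
- Study Setting: recruitment, then testing, then baseline survey, stated to be sequential.
- Recruitment via WeChat: the volunteer screens, and testing is arranged before enrollment.
- Testing overview: an HIV-negative result is a condition of enrollment.
- Survey Content and Follow-Up: the questionnaire is completed at enrollment, hence after the qualifying result.
- Electronic Informed Consent: consent opens that questionnaire.

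The combined order is recruitment, volunteer screening, self-test and result, consent, baseline survey.

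**Step 2: look for text that puts consent earlier.**
- Ethical Considerations requires the form to be read before enrollment. Testing is also before enrollment, so this does not put consent ahead of the test.
- Inclusion criterion 5 requires willingness and ability to consent. It does not say when consent is given.
- Table 2 places recruitment, eligibility screen and consent together at month 0. Its testing row is ticked only at months 6 and 12, so it omits the baseline test and cannot show where that test falls relative to consent.

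Nothing in the text places consent before screening or testing.

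**Step 3: who misses the consent form.** A man who screens HIV-positive is ineligible. He does not reach enrollment, and so does not reach the questionnaire that carries the form.

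**Step 4: effect on the testing indicators.** Let b be the true proportion tested in the 3 months before study contact, and c the proportion of the remaining men who count the entry test when they answer. The recorded baseline is

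b* = b + c(1 − b),

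so the inflation is c(1 − b). If c = 0 (entry test excluded), b* = b. If c = 1, b* = 100% whatever b is, and the change to a follow-up proportion f, which is f − 100%, cannot be positive. The article gives neither b nor c, so the inflation can only be bounded: it lies between 0 and 1 − b.

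**Step 5: an illustrative count.** The Introduction cites HIV prevalence of 3.8% to 4.4% in student MSM. If applicants mirrored that, the number of HIV-positive men tested for every 484 HIV-negative men found would be 484 × p/(1 − p):
- p = 0.038: 484 × 0.038/0.962 = 19.1
- p = 0.044: 484 × 0.044/0.956 = 22.3

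This shows the scale under that assumption and is not an estimate for this study.

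**The case against.** **The order is put together from several sections and is not stated in one place.** The Abstract and Results name surveys before self-tests, the phase list in Study Setting does not mention consent, and Figure 1, which shows participant flow, is not available here. Operating procedures exist that the article does not reproduce. This limits what can be said about practice. It does not remove the conflict, because the sections that speak to order agree with one another, and naming two things together does not order them.

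**A reader might infer that men are tested without any consent.** The documents do not support that. Each man requests the kit himself through a mini-program that has run for over 2 years, tests himself and uploads the photograph himself. That service may have its own consent. The research code is generated at enrollment, so nothing shows that results of screened-out men enter the research data. What remains is that no study consent is described before a test the study requires.

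**A reader might infer that the 127 men already recruited were all tested before consent.** They are reported as having completed both survey and tests, with no order given.

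**A reader might take the row order in Table 2 as evidence.** Rows sharing one column do not encode sequence. Only the missing month-0 testing tick counts, and that is an omission in the table.

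**The baseline effect might be thought slight.** No intervention component is scheduled before month 1, and a recent test cannot change past risk behavior that is being recalled. This is fair for the condom-use and partner items, though a known result could still color how they are reported. It does not help the testing indicators, whose 3-month window takes in the entry test.

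**Conclusion.** The concern holds on the article's own text. Screening and the study-required self-test precede the only study consent described, and the baseline survey follows the test result. This is a stated position of consent that conflicts with a stated sequence, so it is more than detail left to a fuller document.

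By design the order applies to all 484 planned participants and to everyone screened but not enrolled. How many men have actually been tested before consent cannot be known from the article. The figure of about 19 to 22 HIV-positive men is illustrative only: men who know their status may not apply, since the announcements state the inclusion criteria.

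For the two testing indicators, the baseline is inflated by anything from nothing to the full distance to 100%, depending on whether the questionnaire excludes the entry test. The questionnaire is in an appendix that is not shown. The bias masks a gain. Effects on knowledge and willingness items are possible, but their size cannot be judged from the document.

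The conclusion assumes that no earlier study consent exists outside the text and that the phases run in the listed order.

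**What to change.** 1. Place the existing electronic consent before eligibility screening and testing, and have it cover screening, self-testing, sharing of results and the survey.
2. Have the baseline questionnaire completed before the kit is dispatched, or word the testing items to exclude the study's entry test. Holding back the result until after the survey would not work, because the user can read the cassette himself within 15 minutes. Finishing the survey before dispatch also takes the known result out of the knowledge and willingness answers, though not the first contact with the volunteer.
3. Reconcile Ethical Considerations, Study Setting, Recruitment via WeChat, Electronic Informed Consent, and Survey Content and Follow-Up so that all give the same order. Add the month-0 tick to the testing row of Table 2.
4. State whether the testing service takes its own consent and what that covers.
5. For men already recruited, report how many were tested before study consent, and whether their baseline testing answers could include the entry test.

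The cost is a minor ethics amendment and the relocation of an existing web form. Some consented men will complete the survey and then be excluded on the HIV test, so sensitive answers will be held for men outside the cohort, and the consent should say so. Recruitment is under way, so delay adds to the number affected.

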### Generation of Unique Participant ID and Data Security

To ensure participant anonymity while allowing for longitudinal data linkage, a de-identified participant code will be generated for each individual at enrollment. The participant ID consists of a randomly generated alphanumeric string created through an independent encryption algorithm, ensuring that no elements of phone numbers, timestamps, or other personally identifiable information (PII) are embedded in the code. The mapping file linking IDs with PII will be stored separately in an encrypted database accessible only to authorized Chengdu CDC data managers.

All study data are managed within a comprehensive data protection and security framework, consistent with national and international privacy standards. PII (such as phone numbers, WeChat IDs, and mailing addresses) is collected solely for operational purposes and stored separately from deidentified research data. Both databases are encrypted at rest and during transmission using the Advanced Encryption Standard (AES-256) encryption protocol implemented within the Chengdu CDC secure data environment.

A Data Protection Impact Assessment was performed to identify potential privacy risks and define mitigation strategies, including data-flow mapping, encryption and storage measures, access-control policies, retention and deletion schedules, and oversight procedures.

Access to data is governed by role-based access control, ensuring that each staff member only accesses the data required for their function. Multifactor authentication (eg, password+phone verification) is required for system login. All access and data modification activities are recorded through automated audit logs, which are periodically reviewed by the Chengdu CDC data security officer.

In accordance with the approved data retention and deletion schedule, PII will be retained for up to 6 months after study completion and then permanently deleted from all servers. Deidentified research data will be securely stored for 5 years for potential secondary analysis and subsequently removed after encrypted archiving.

These combined administrative, technical, and procedural safeguards ensure participant anonymity and protect the confidentiality, integrity, and traceability of all data throughout the study lifecycle.

### Survey Content and Follow-Up

Participants will complete a baseline questionnaire upon enrollment, which collects detailed information on sociodemographic characteristics, sexual behaviors, HIV-related knowledge, attitudes, practices, and other relevant behavioral factors (see Multimedia Appendix 3 for details).

Follow-up surveys will be administered at two time points post-intervention: 6 months and 12 months. The content of the follow-up questionnaires will be identical to that of the baseline survey to enable assessment of changes over time (see Multimedia Appendix 4 for follow-up questionnaire content). Data collection instruments and operational manuals have been standardized to ensure consistency in measurement and facilitate reproducibility across different investigators.

### Intervention Process

#### Developing Intervention Package

The intervention will be conducted entirely online over a 12-month period. Under the guidance of HIV prevention experts and CBO trainers, we have developed a comprehensive and targeted intervention package for participants. This package includes a standardized online intervention workflow (Figure 1), evidence-based web-based content, and accessible links to self-testing kits and referral services. A detailed schematic of the participant flow and multilevel intervention process is presented in Figure 1. The diagram depicts the sequential stages of recruitment, screening, enrollment, baseline assessment, intervention delivery, and follow-up. Detailed standard operating procedures have been developed to standardize the delivery frequency, message content, and volunteer-participant interactions, ensuring consistency across all intervention components. To ensure consistency and standardization in the delivery of peer-led interventions, the project implements a multilayered training, certification, and supervision system.

#### Standardized Training Curriculum

All peer volunteers undergo a unified, structured training program jointly conducted by the Chengdu CDC and partner CBOs. The training covers HIV prevention knowledge, motivational interviewing skills, online communication protocols, and ethical considerations (confidentiality and noncoercive engagement).

**Figure 1. F1:**
[figure not shown]
Participant flow and intervention process of the study. Rounded rectangles denote the core procedural stages of participant enrollment and intervention and follow-up. Stadium-shaped nodes indicate critical follow-up checkpoints. Circles represent study end points, including completion and loss to follow-up. Square boxes indicate detailed information units (eg, eligibility criteria and intervention components). Solid arrows indicate participant progression through the study procedures, while dashed arrows indicate attrition paths. MSM: men who have sex with men.

#### Posttraining Assessment and Certification

After training, each volunteer must pass a competency assessment that evaluates communication, adherence to intervention procedures, and knowledge of referral pathways. Only volunteers who pass this assessment are certified to conduct interventions.

#### Guideline Support

Each volunteer receives a “Guidelines for Internet-Based HIV Interventions,” which includes frequently asked questions and recommended responses. This guideline serves as a reference to ensure uniform content delivery and quality control during intervention sessions.

